##### Blood samples

Blood samples are collected to measure biomarkers of inflammation and vitamin D at baseline. During T0 and T1, two tubes of 10 mL of blood will be collected. One of these tubes will be saved in the biobank NKI-AVL. The other will be used to assess vitamin D and the following inflammatory biomarkers in duplicate by ELISA: IL-1RA, hsIL-6, sTNF-RII, and hsCRP. Vitamin D has been associated with current levels of fatigue [60–62]. The before-mentioned biomarkers have previously been associated with fatigue in patients with cancer [35, 63]. The level of these biomarkers, as well as the change in biomarker levels will be used as parameters for the statistical analysis.

### Data management

The original signed informed consent forms are stored at the department of the participating institute where the participant is recruited. All participants receive a unique participant number, in order to code their outcome measures without the risk of harming anonymity. Participants can choose to complete an online or pen-and-paper version of the questionnaire. Paper versions of completed questionnaires and a (copy of) the signed informed consent forms are stored at the Division of Psychosocial Research and Epidemiology of the Netherlands Cancer Institute separately. Online completion of questionnaires will take place via an online secured (HTTPS) research tool, called Explora Zorg, which is specifically developed for research in Dutch health care. Each participant has a personal log-in code. Completed paper versions of the questionnaires will be entered in this online system by the research assistant.

The information given online by patients is accessible to the study staff only, via a secured code. This code is known by the principal investigator (EB), the study coordinator (DS), and the research assistant (JG). The principal investigator will safeguard the key to the code. The collected data in this research tool is saved on the secured database of the Netherlands Cancer Institute on a monthly basis.

Blood and saliva samples of all participants are stored at the general clinical laboratory of the Netherlands Cancer Institute. Each sample is coded with a unique participant number. Date and time of sampling are reported on the samples.

### Statistical methods

#### Sample size calculation

The MFI is the primary outcome on which sample size calculations are based. With a sample of 128 patients (*n* = 64 per group), the study will have an 80% power to detect an Cohen’s effect size of 0.5 for the main effect of light therapy on fatigue with a *p*-value set at 0.05 (power calculation with G*power 3 [64]). Cohen’s effect size of 0.5 means a 0.5 standard deviation difference on the primary measurement outcome, which is considered to be a clinical meaningful difference [65]. Participants who discontinue light therapy but complete questionnaires will be included in the intention-to-treat analysis.

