#### Outcome measures

The Multidimensional Fatigue Inventory (MFI) [41], a VAS-scale for fatigue [42] and the Work and Social Adjustment Scale (WSAS) [43] are the primary outcome measure of this study. Secondary outcome measures include: Pittsburg Sleep Quality Index (PSQI) [44], wrist actigraphy [45], Center for Epidemiological Studies – Depression scale (CES-D) [46], State-Trait Anxiety Inventory-6 items (STAI-6) [47], Medical outcome studies short form (SF-36) [48], Medical Outcomes Studies Cognitive function scale (MOS-CF6) [49], MD Anderson Symptom Inventory (MDASI) [50], Psychomotor Vigilance Task (PVT) [51], 15 words task [52], digit span task [53], cancer worry scale (CWS) [54], fatigue catastrophizing scale (FCS) [55], Self-efficacy scale 28 (SES-28) [56], salivary cortisol and melatonin, and inflammatory biomarkers. Detailed descriptions of these outcome measures are provided in Table 1.

**Table 1 Tab1:** Study outcome measures and corresponding questionnaires

Variable	Questionnaire	Number/type of items	Time frame	Score range	Psychometric details
Primary outcomes					
Cancer related fatigue	MFI [41]	20 four-point Likert scale	Past few days	Subscale scores: 4–20; higher scores indicate more fatigue	Subscales: general fatigue, mental fatigue, physical fatigue, reduced motivation, reduced activity. Cronbach’s alpha: 0.84
	VAS-scale [42]	1 eleven-point Likert scale	This moment	0–10; higher scores indicate more fatigue	
Restrictions caused by fatigue	WSAS [43, 70]	5 nine-point Likert scale	Influence of fatigue on daily life	0–40; higher scores indicate higher levels of disability	Cronbach’s alpha: > 0 .79
Secondary outcomes					
Sleep quality	PSQI [44]	19 four-point Likert scale and open-ended questions	Past month	Total score: 0–21 Subscale scores: 0–3; higher scores indicate more acute sleep disturbances	Subscales: subjective sleep quality, sleep latency, sleep duration, habitual sleep efficiency, sleep disturbances, use of sleeping medication, daytime dysfunction. Cronbach’s alpha: 0.83
Depression	CES-D [46, 71]	20 four-point Likert scale	Past week	0–60; higher scores indicate greater depressive symptoms	Cronbach’s alpha: 0.85–0.90
Anxiety	STAI-6 [47]	6 four-point Likert scale	This moment	20–80; higher scores indicate increased anxiety	Cronbach’s alpha: 0.83

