#### Statistical analyses

Data will be analysed using the Statistical Package for the Social Sciences (SPSS). Although we endeavour to check all questionnaires upon their return and call participants to complete missing items, some data might still be missing. Missing values will be imputed according to the manual of the questionnaire. In general, descriptive statistics will be computed for the outcome variables, potential covariates and demographic variables. Bivariate analyses will be undertaken to explore associations between outcome and potentially confounding variables (e.g. season, diagnosis, years since diagnosis) using correlations (for continuous variables) and Chi-square tests (for categorical variables).

Group differences in change in fatigue during the trial will be investigated using a mixed effect growth model with random intercept and slope, nested within site (clusters of different hospitals). This approach takes into account the within and between person variability, and deals adequately with missing data [66]. If baseline differences are identified despite randomisation, these variables will be accounted for in the model. In case of non-ignorable dropout we will correct the model for different patterns of missing values [67]. All analyses will be done on an ´intention to treat´ basis. Additional explorative analyses will be done on a ´per protocol´ basis.

The mixed effect model approach described for change in fatigue will also be used to determine treatment effects of continuous secondary outcome measures. To evaluate between-group differences in categorical secondary outcome measures, we will use generalized estimating equations (GEE) for longitudinal data. This approach accounts for correlated within subject responses, allows for not normally distributed variables and deals adequately with missing data [67–69]. Since there are multiple outcomes, the *p*-values for each model will be adjusted for multiple comparisons.

Within the intervention group we will explore which variables are predictive for the efficacy of light therapy in reducing fatigue. A mixed effect model for longitudinal data will be used with fatigue as dependent variable and the following independent variables: sleep quality, depression, anxiety, cognitive complaints, quality of life, and biological circadian rhythms. The *p*-values will be adjusted for multiple testing.

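### One primary outcome or three is left unresolved, and the stated 80% power holds only for a single unadjusted test at 0.05

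*Protocol article*

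**What the plan says.** Three places in the protocol article bear on this.

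- **Sample size calculation.** The MFI is called the primary outcome on which the calculation rests. "With a sample of 128 patients", 64 per group, "the study will have an 80% power to detect an" effect size of 0.5, with the p-"value set at 0.05" ("power calculation with G*power 3"). The effect size "means a 0.5 standard deviation difference on the primary measurement outcome", in the singular.
- **Outcome measures and Table 1.** The MFI, a fatigue VAS and the WSAS together "are the primary outcome measure of this study", and Table 1 lists all three under primary outcomes. For the MFI it gives a score range per subscale and no total: "Subscales: general fatigue, mental fatigue, physical fatigue, reduced motivation, reduced activity".
- **Statistical analyses.** Change in fatigue is compared between groups with a mixed effect growth model. The next paragraph turns to continuous and categorical secondary outcomes. It closes by saying that, because there are multiple outcomes, the p-values "for each model will be adjusted for multiple comparisons". It names neither the method nor the set of tests that the adjustment covers.

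**The concern.** The sample size section assumes one outcome and one test. The outcomes section sets up three primary instruments, one of which has five scores. Nothing ranks them, and nothing says which result or combination of results would count as success.

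This matters for the main efficacy claim in both directions. If the announced adjustment applies to the primaries, each is tested at a stricter level than the one behind the 80%, and a null result is more likely than the protocol suggests. If it does not apply, several primaries are each tested at 0.05, and a positive result on any one of them carries more than a 5% risk of being false. A reader of the results could not tell which situation applied.

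**Working it through.** **Inputs from the protocol:** n = 64 per group, allocation 1:1, d = 0.5, α = 0.05, three primary instruments, five MFI subscales.

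**Assumptions, because the protocol does not state them:** two-sided tests; Bonferroni or Holm as the adjustment; equal correlation ρ between endpoints; for Holm, a true effect of 0.5 SD on every endpoint.

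**Step 1: reproduce the stated figure.** For a two-sample t-test, the noncentrality is d·√(n/2) = 0.5·√32 = 2.828, with 2·64 − 2 = 126 degrees of freedom. The two-sided 0.05 critical value is 1.979. Power from the noncentral t is 80.1%. With 63 per group it is 79.5%, so 64 is the exact minimum. A one-sided test would give 87.9%. The protocol's figure is therefore one two-sided test at 0.05, with nothing in reserve for multiplicity.

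**Step 2: the primaries are adjusted, Bonferroni.** Same formula at α/k:

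| Primary tests k | α/k | Critical t | Power per score | n per arm for 80% |
|---|---|---|---|---|
| 1 | 0.0500 | 1.979 | 80.1% | 64 |
| 3 (three instruments) | 0.0167 | 2.426 | 65.6% | 86 |
| 7 (five subscales + VAS + WSAS) | 0.0071 | 2.735 | 53.9% | 102 |

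**Step 3: the primaries are adjusted, Holm.** The ordered p-values are compared with 0.05/k, 0.05/(k−1), …, 0.05, stopping at the first failure. This was simulated with normal test statistics of mean 2.828 and ρ from 0 to 0.9. Average power per score is 73–76% for three tests and 64–68% for seven, with the higher values at low correlation. The normal approximation is slightly generous: it gives 80.7% for the single test against the exact 80.1%.

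**Step 4: the primaries are not adjusted.** Power per score stays at 80.1%. The chance of at least one false positive for three independent tests is 1 − 0.95³ = 14.3%. By simulation it is about 12.5% at ρ = 0.5 and 11% at ρ = 0.7. For seven tests the independent value is 1 − 0.95⁷ = 30.2%, falling to about 18% at ρ = 0.7.

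**Step 5: other success rules, none of which the protocol states.** If any one of three Bonferroni-adjusted primaries sufficed and all had a 0.5 SD effect, power would be about 92% at ρ = 0.3, 83% at ρ = 0.7 and 76% at ρ = 0.9. If all three had to reach 0.05, it would be about 58% at ρ = 0.3, rising to 73% at ρ = 0.9.

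**The case against.** The adjustment sentence closes a paragraph on secondary outcomes. The fatigue model has its own paragraph, which mentions no adjustment. On that reading the 80% per test is untouched. The sample size section also speaks of the primary outcome in the singular, so one can read the MFI as the lead outcome. Choice of subscale and method of adjustment are things an unseen analysis plan may settle. Finally, Bonferroni is the pessimistic end, and the planned analysis is a mixed model over four time points, not a t-test.

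Much of this stands, and it limits what can be claimed. A reader might infer that the trial is certain to deliver less than 80% power. The text does not support that, because it does not establish that the primaries are adjusted. A reader might also take seven primary tests as fixed. Table 1 describes the instruments; the absence of a total score there does not commit the trial to five separate MFI tests. Nor does the protocol define one large family that pools primaries with secondaries. And the mixed model could move power in either direction.

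What does not fall away is the disagreement between sections. An analysis plan can add a method of adjustment, but the number of primaries and the error level behind the sample size are both stated here, and they do not match. Reading the adjustment as secondary-only does not rescue the position: it keeps the power and gives up error control over the three named primaries. Reading the MFI as sole primary contradicts the Outcome measures section and Table 1, and still leaves open which MFI score is meant.

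**Conclusion.** The point holds as an unresolved primary family. The sample size arithmetic is correct for one test. As long as three primaries stand, neither reading of the adjustment sentence makes 80% power at 5% error a description of the primary analysis:

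- **Primaries adjusted:** power for a given score is about 66% (Bonferroni) to 73–76% (Holm) with three tests, or about 54% to 64–68% if the MFI subscales make it seven.
- **Primaries not adjusted:** the family-wise error is about 11–14% for three tests.

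These figures rest on two-sided tests, 64 analysed per arm, a t-test approximation to the planned model and, for Holm, a 0.5 SD effect on every endpoint. The error range assumes correlations between 0.7 and 0. The three-test figures follow from the protocol's own list of instruments; the seven-test figures apply only if the subscales are tested separately.

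**What to change.** Before unblinding:

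1. Name one MFI score and one treatment contrast from the planned mixed model as the single primary, tested two-sided at 0.05. The calculation for 128 patients and 80% power then stands as written.
2. Test the VAS and the WSAS next, either in a fixed sequence after the primary or with Holm.
3. Place the other MFI subscales and the secondary outcomes in a separate family with its own stated adjustment, and say explicitly that the adjustment sentence refers to that family.
4. Make the Outcome measures section, Table 1 and the sample size section agree.

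If all three instruments are kept as primaries, state the adjustment method and the success rule, and restate the power for that method and number of tests.

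The cost is a protocol amendment and a registry update. Recruitment began in August 2017, so the change should be dated and shown to precede unblinding. No extra patients or data are needed.

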#### Statistical analyses

Data will be analysed using the Statistical Package for the Social Sciences (SPSS). Although we endeavour to check all questionnaires upon their return and call participants to complete missing items, some data might still be missing. Missing values will be imputed according to the manual of the questionnaire. In general, descriptive statistics will be computed for the outcome variables, potential covariates and demographic variables. Bivariate analyses will be undertaken to explore associations between outcome and potentially confounding variables (e.g. season, diagnosis, years since diagnosis) using correlations (for continuous variables) and Chi-square tests (for categorical variables).

Group differences in change in fatigue during the trial will be investigated using a mixed effect growth model with random intercept and slope, nested within site (clusters of different hospitals). This approach takes into account the within and between person variability, and deals adequately with missing data [66]. If baseline differences are identified despite randomisation, these variables will be accounted for in the model. In case of non-ignorable dropout we will correct the model for different patterns of missing values [67]. All analyses will be done on an ´intention to treat´ basis. Additional explorative analyses will be done on a ´per protocol´ basis.

The mixed effect model approach described for change in fatigue will also be used to determine treatment effects of continuous secondary outcome measures. To evaluate between-group differences in categorical secondary outcome measures, we will use generalized estimating equations (GEE) for longitudinal data. This approach accounts for correlated within subject responses, allows for not normally distributed variables and deals adequately with missing data [67–69]. Since there are multiple outcomes, the *p*-values for each model will be adjusted for multiple comparisons.

Within the intervention group we will explore which variables are predictive for the efficacy of light therapy in reducing fatigue. A mixed effect model for longitudinal data will be used with fatigue as dependent variable and the following independent variables: sleep quality, depression, anxiety, cognitive complaints, quality of life, and biological circadian rhythms. The *p*-values will be adjusted for multiple testing.

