### Study procedure

All participants complete a battery of self-report questionnaires and wear a wrist actigraph at four different measurement points (T0: baseline; T1: directly after 3,5 weeks of light therapy; T2: 3 months after light therapy; T3: 9 months after light therapy). The first (T0) and second (T1) measurement points include a visit to the hospital to provide participants with materials and instructions, to perform cognitive tests, and to collect blood (during the visit) and saliva (on day 8 and 36) samples. Figure 2 shows a schematic diagram of a participant’s timeline.

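### Use of baseline fatigue in the primary growth model depends on an observed imbalance; fixing it in advance would recover precision at almost no cost

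*Protocol article*

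**What the plan says.** Under Statistical analyses, the protocol article states the primary comparison: "Group differences in change in fatigue during the trial will be investigated using a mixed effect growth model with random intercept and slope". The same paragraph gives its only rule on baseline: "If baseline differences are identified despite randomisation, these variables will be accounted for in the model". The next paragraph extends the mixed-model approach to continuous secondary outcomes.

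Study procedure sets four occasions: "T0: baseline; T1: directly after 3,5 weeks of light therapy; T2: 3 months after light therapy; T3: 9 months after light therapy". Fatigue is thus scored once as a baseline and three times afterwards. Under Randomization, the balancing factors are diagnosis, time since diagnosis and gender; baseline fatigue is not among them.

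Sample size calculation claims 80% power with 64 per group "to detect an Cohen’s effect size of 0.5 for the main effect of light therapy on fatigue", and explains that "Cohen’s effect size of 0.5 means a 0.5 standard deviation difference on the primary measurement outcome". The effect is scaled to the SD of the outcome. It is not said to be scaled to the SD of change, and no credit is taken for baseline.

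**The concern.** A growth model for change with a random intercept most naturally takes T0 as the first response. In its usual form (group, time, group-by-time) each arm has its own baseline mean, and the treatment effect is a difference in change from that mean. A random intercept does not make this a baseline-adjusted comparison. With complete balanced data, the group-by-time estimate is the difference between arms in mean individual change or slope.

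Randomisation guarantees that the true T0 means are equal, so estimating them separately discards information. That information is there whether or not an imbalance shows up, yet the stated rule uses it only when one does. At stake are precision and prespecification: the primary model would depend on a look at the data, and the group difference would be estimated with more variance than necessary.

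**Working it through.** **Inputs from the protocol article.** 64 per arm; d = 0.5 on the outcome SD; alpha 0.05 (sidedness not stated; two-sided fits). Visits lie at 0, about 0.8, 3.8 and 9.8 months (3.5 weeks, then 3 and 9 months later).

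**Assumed, because the documents give no figure.** rho = 0.3 to 0.7; random-slope variance, scaled to T3, from 0 to 2 times the residual variance; intercept and slope uncorrelated.

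**1. The stated power.** A two-sample t-test (non-central t, two-sided 0.05, d = 0.5, 64 per arm) gives 80.1%. The stated 80% reproduces. A one-sided test would give 87.9% and does not fit.

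**2. A single T1 contrast.** Per unit outcome variance, the difference in change has variance factor 2(1-rho). With baseline adjustment or a common T0 mean it is 1-rho². The ratio is (1+rho)/2, so the cut is (1-rho)/2. Power uses d/√(variance factor).

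| rho | change factor | adjusted factor | cut | power, change | power, adjusted |
|---|---|---|---|---|---|
| 0.3 | 1.40 | 0.91 | 35% | 66% | 84% |
| 0.5 | 1.00 | 0.75 | 25% | 80% | 90% |
| 0.6 | 0.80 | 0.64 | 20% | 88% | 94% |
| 0.7 | 0.60 | 0.51 | 15% | 95% | 98% |

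At rho = 0.5 the change factor is 1, which matches the comparison used for sizing. Below 0.5 it exceeds 1 and power drops under 80%; above 0.5 the reverse holds. Generalised least squares on four visits under compound symmetry gives the same ratios: at rho 0.5 the T1 variance is 0.0313 with free baselines and 0.0234 with a common one, and 0.0234/0.0313 = 0.75.

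**3. The linear slope over T0-T3, closer to the planned model.** Generalised least squares with fixed effects (intercept, time, group, group-by-time) against the same model without the group term gives these cuts in the variance of group-by-time:

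| rho | time in months | time as visit number |
|---|---|---|
| 0.3 | 11-24% | 19-40% |
| 0.5 | 7-15% | 13-26% |
| 0.7 | 4-8% | 7-15% |

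The larger figure in each cell is for zero slope variance, the smaller for twice the residual variance. A negative intercept-slope correlation raises the cut: with correlation -0.3, intercept share 0.5 and slope variance 0.15, the months ratio moves from 0.874 to 0.795, so the cut goes from 13% to 21%.

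In power terms, starting from 80%, new power is Φ((0.842 + 1.960)/√(1-cut) - 1.960). At rho 0.5 with time in months this is 83% for a 7% cut and 86% for a 15% cut, a gain of about 3 to 6 points.

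**4. Does the conditional rule recover this?** Not if it is applied by adding T0 fatigue as a main effect while T0 stays in the response. A covariate that is constant over time cancels from within-person change. In a simulated set of 128 × 4 observations, group-by-time was -0.05674 both without and with that covariate, but -0.05184 with a common baseline mean. Other implementations, such as a baseline-by-time term or T0 as covariate only, would behave differently; the wording does not say which is meant.

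**The case against.** **The defect is partly inferred.** The article names a model family and a target. It lists no fixed effects and does not say that arms have separate T0 means. A growth model with time and group-by-time only would already be the common-baseline model. Fixed effects are often left to a full protocol or analysis plan, which is not shown. This stands, so the loss is conditional on the natural reading. The imbalance-triggered rule, however, is stated in the article and is not mere missing detail.

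**A reader might infer that baseline fatigue is never adjusted for.** The documents do not support that. The conditional rule does not exclude fatigue; the accurate criticism is that its use is data-dependent.

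**A reader might carry the 10-point gain at rho 0.5 over to the primary analysis.** That figure is for a single T1 contrast. For a linear slope in months the gain is smaller, and the coding of time is not stated.

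**A reader might conclude that the trial has less than 80% power.** That needs rho below 0.5, which the documents do not give. Selecting fatigued patients could lower rho, but entry is by either of two scales, so neither is truncated for everyone. Persistent fatigue re-measured after 3.5 weeks could well correlate above 0.5.

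**A chance baseline difference is not a further harm.** The T0 mean difference has SD √(2/64) = 0.177, so 0.2 SD or more has probability about 26%. At rho 0.5 it shifts the change estimate by (1-0.5) × 0.2 = 0.10 SD. This is the same random variation already counted in step 2. Across randomisations the estimator is unbiased.

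**Conclusion.** The point holds as one of efficiency and prespecification. The article makes use of baseline variables, fatigue included, conditional on an identified imbalance. If T0 is a response with arm-specific means, precision is given away. For rho of 0.3 to 0.7 and the slope variances assumed, the avoidable variance is about 4-24% for a slope in months, 7-40% for a slope by visit number, and 15-35% for a single T1 contrast. The gain shrinks as rho rises, to about 2 power points at T1 when rho is 0.7.

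Nothing here shows bias or an error in the sample size: the stated 80% reproduces. If the sponsor already intends a common baseline mean, saying so settles the matter.

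**What to change.** State in the analysis section that the primary model will always do one of the following, whether or not an imbalance is seen:

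- keep T0 in the response with one common baseline mean for both arms, that is, no group main effect at T0; or
- model T1-T3 only, with T0 fatigue as a pre-specified covariate interacting with time.

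Take baseline fatigue out of the rule on identified baseline differences. Apply the same choice to each continuous secondary outcome measured at T0, using that outcome's own T0 value.

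The cost is a sentence or two of text and a small change of model syntax in SPSS. No new data or patients are needed. The covariate form uses a few degrees of freedom. The common-mean form relies on T0 being unaffected by allocation, which randomisation and a pre-treatment T0 secure.

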### Randomization

Equally distributed across all four seasons, participants are randomized to either an intervention group (*n* = 64) or a comparison condition (*n* = 64) using the minimization technique at a 1:1 ratio. Randomization is stratified for diagnosis (HL; DLBCL), time since diagnosis (< 5 years; 5–10 years; 11–20 years; > 20 years) and gender (male; female). Randomization is outsourced to an independent party, using the randomization programme ALEA. The output determines which lamp (with BWL or with DWL) is offered to each participant. This lamp will be part of the content of a bag offered to the research assistant who visits the participants. In this way, both the research team and the participants are blinded to the allocated condition. The randomization code will only be broken if a patient reports severe adverse side effects as a result of the light intervention.

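### Covariates are to be chosen from observed baseline differences, although allocation is by minimisation, which is designed to prevent such differences in the factors that the model should carry

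*Protocol article*

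**What the plan says.** - **Allocation** (Randomization): patients are allocated "using the minimization technique at a 1:1 ratio", 64 per arm. The factors are introduced with "Randomization is stratified for diagnosis (HL; DLBCL), time since diagnosis" (four categories) and end with gender. Season is mentioned separately: "Equally distributed across all four seasons, participants are randomized to either an intervention group". It is not in the list of factors.
- **Primary model** (Statistical analyses): group differences in change in fatigue are tested in a "mixed effect growth model with random intercept and slope, nested within site (clusters of different hospitals"). Site is the only design variable named.
- **Covariate rule** (same section): "If baseline differences are identified despite randomisation, these variables will be accounted for in the model".
- **Exploration** (same section): "Bivariate analyses will be undertaken to explore associations between outcome and potentially confounding variables", with season, diagnosis and years since diagnosis as examples. The text does not say that these results decide what enters the model.

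**The concern.** The covariate rule works against the allocation method. Minimisation acts on diagnosis, time since diagnosis and gender so that they do not differ between arms. A rule that admits only variables that do differ will therefore usually pass over these three. What it admits will mostly be variables that minimisation did not control and that differ by chance, whether or not they are related to fatigue.

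Two things are at stake. First, the primary model is not known until the baseline data have been inspected, and neither the meaning of a difference nor the set of variables to examine is fixed. That leaves the analyst a choice. Second, when allocation is balanced on a factor that predicts the outcome, the treatment estimate varies less than an analysis without that factor reports. Standard errors are then too large, and power is lost.

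**Working it through.** **1. The plan's own figure.** Inputs from Sample size calculation: 64 per group, effect size 0.5 SD, alpha 0.05 (taken as two-sided), power 80%. The noncentral t distribution gives power 0.801 at 64 per group and 0.795 at 63, so 128 is reproduced. That calculation assumes no covariates.

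**2. What the rule selects.** Assumptions: minimisation with a biased coin of 0.8; seven candidates (the three allocation factors, season and three other baseline variables); a difference means p < 0.05. The rule then adjusted for something in about 18% of simulated trials of 128 patients. Four freely varying variables tested at 5% would alone give 1 − 0.95^4 = 0.185. So the selections are accounted for by the variables that minimisation does not control.

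**3. Size for a balanced factor left out.** Let R² be the share of variance in the analysed quantity that the factors explain. With near-perfect balance:

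- width ratio (reported / true) = 1/√(1 − R²)
- actual type I error = 2 × [1 − Φ(1.96/√(1 − R²))]

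| R² (assumed) | Width ratio | Type I error |
|---|---|---|
| 0 | 1.00 | 0.050 |
| 0.05 | 1.03 | 0.044 |
| 0.10 | 1.05 | 0.039 |
| 0.20 | 1.12 | 0.028 |
| 0.30 | 1.20 | 0.019 |

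**4. Which variance counts in the planned model.** The model tests change and has a random intercept, which absorbs effects on level. With complete data, the group-by-time contrast can be checked on each person's change. Simulated ratios of unadjusted to adjusted standard error, with a balanced factor explaining 30% of level throughout:

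| Share of change explained (assumed) | SE ratio |
|---|---|
| 0 | 1.00 |
| 0.05 | 1.03 |
| 0.10 | 1.06 |
| 0.30 | 1.20 |

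So R² in step 3 must be read as the share of *change* explained.

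**5. Does the baseline-difference rule repair this?** Simulated for one outcome at a single time point, as an illustration rather than the planned model (season R² 0.05):

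| Factor R² | Analysis | Reported / true SE | Type I error | Power at d = 0.5 |
|---|---|---|---|---|
| 0.1 | Baseline-difference rule | 1.06 | 0.034 | 0.81 |
| 0.1 | Prespecified factors and season | 0.995 | 0.052 | 0.85 |
| 0.3 | Baseline-difference rule | 1.21 | 0.017 | 0.85 |
| 0.3 | Prespecified factors and season | 1.00 | 0.049 | 0.93 |

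With no prognostic value (R² = 0, season 0), both give 0.054 and the rule does no harm to the error rate.

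**6. Which terms are needed.** In a random intercept-and-slope model (128 patients, four times, balanced factor explaining 30% of slope variance), the group-by-time standard error was 0.0746 without the factor, 0.0746 with it as a main effect, and 0.0659 with factor-by-time. 0.0746/0.0659 = 1.13. The 30% here is a share of slope variance, whereas step 4 takes shares of the whole observed change, so 1.13 need not match 1.20. The point is that a main effect alone recovers nothing for the slope contrast.

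**The case against.** The strongest reply is that the article condenses a fuller plan. It does not say that the allocation factors enter *only* when they differ, and a complete covariate list is commonly left to the analysis plan. This stands against any complaint that the list is short. It does not answer the point about the rule, which the article states and which would have to be changed, not just filled in.

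The second reply is that the planned model limits the harm. This stands in full. The random intercept removes effects on level, site is already in the model, the article gives no figure for how well the factors predict change, and any error is conservative.

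Some stronger readings are tempting but not supported:

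- **Season.** A reader might treat it as another balanced factor whose omission makes the standard error invalid. It is not a listed minimisation factor. Unless it was actively balanced, leaving it out costs precision and no more.
- **The bivariate analyses.** They might be read as a second gate into the model, and the chi-square tests criticised as unsuited to a continuous fatigue score. The text only says that associations will be explored. It speaks of the outcome in general, and the section also plans categorical secondary outcomes.
- **Chance imbalance.** With 20 independent baseline tests at 5%, 1 − 0.95^20 = 0.64 is the chance of at least one difference. The article fixes neither the number of tests nor their independence.
- **Baseline fatigue.** A reader might credit adjustment for it with a large further gain in power. T0 is already one of the four measurement points of a model of change, so a gain computed for a single follow-up comparison does not carry over.

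**Conclusion.** The point holds as a fault in a stated rule. The baseline-difference rule makes the primary model data-dependent and will usually omit the factors that governed allocation.

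Its effect on the intervals is conditional: about 3%, 6% and 20% too wide if the allocation factors explain 5%, 10% and 30% of change in fatigue, and none if they explain level only. This rests on assumed shares, near-perfect balance and complete data. It would be wrong to conclude that the trial's error bars are certain to be wrong, or that false positives are inflated; the documents support neither. The planned 128 patients are unaffected. The change is worth making because it removes analyst discretion at almost no cost, not because the trial's validity is in danger.

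**What to change.** For the efficacy models:

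1. Delete the baseline-difference rule.
2. Prespecify diagnosis, time-since-diagnosis category and gender with their time interactions, whatever the observed balance. If T1 to T3 are modelled with the baseline value as a covariate, main effects are enough.
3. Add season of light-therapy start in the same way, as a precision covariate.
4. Use baseline fatigue either as a response or as a covariate, not both.
5. Report baseline imbalance descriptively, and keep any other covariate for a labelled sensitivity analysis.

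The cost is one paragraph, fixed before unblinding. All the variables are already collected. The minimisation factors use 1 + 3 + 1 = 5 degrees of freedom and season uses 3, so 8 in all, or about 16 with time interactions, with 128 patients.
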